## **16.5 Data handling**

All data will be listed. Whenever applicable all tables, figures and listings will identify patients using the patient identification (i. e. randomisation-number) and time of evaluation. For data collected prior to randomization, this will be done likewise (i. e. use of subsequently obtained randomisation number)

The actual population presented in a table/figure/listing will be mentioned in the headings.

Tables and listings will be produced in accordance with the principles outlined by the ICH E3 guideline.

### Handling missing data and outliers

Every effort will be made to collect all data points in the study. The amount of missing data will be minimized by appropriate management of the randomized, prospective, trial, proper screening of subjects, and training of participating investigators and other authorized staff (e.g. nurses), monitors and study co-ordinator. Since all patients who are randomized will be included in the primary analysis, in those instances where data are missing, missing values will not be imputed.

Missing data in tables and listings will be handled as missing data by inserting the symbol '.

Outliers may be identified using stem-leaf plots and frequency distributions, Scatter and box plots may be also generated for outlier identification. For normally distributed data, values more than three standard deviations away from the mean will be considered outliers. Transformation of the data to mitigate the influence of outliers may be considered. If outliers remain, additional analyses excluding these values will be done and discussed in the report.

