
\* if not otherwise mentioned measurements of secondary variables on ICU will be performed until fit-for-discharge from ICU criteria are fulfilled or until postoperative day 5 (including), whatever occurs first.

Efficacy:

- Haemodynamics
  - SAP, DAP, MAP, HR, CVP, CI, SV, SVR
  - cumulative dose of norepinephrine (mcg/h)
  - intrathoracic blood volume index (ITBVI) and extravascular lung water index (EVLWI), (PICCO)
- Time on ventilator (*measured from intubation in hours; the need of reintubation will be documented*)
- Requirements of postoperative ventilatory support (PCV, CPAP)
- Nursing Delirium Screening scale (NuDesc) – *measurement three times daily on ICU\**
- gastrointestinal parameters - (*measurement daily from post-op day +1 until fulfilment or until end of study, whatever occurs first*)
  - time until bowel movements (on auscultation)
  - time until full oral nutrition
  - time to first flatus
  - time to first defecation
  - intraabdominal pressure *measured baseline (after induction of anaesthesia), at the end of surgery (still in operating theatre before extubation), 6 hours after surgery, 1st post-operative day in the morning*
- SOFA, SAPS II, APACHE II Scores – *surveyed once daily on ICU\**
- length of stay in ICU/IMCU (fulfillment of ICU/IMCU release criteria according to the Aldrete Score, Aldrete 1995) *surveyed on admission to ICU, 1st postoperative day in the morning, at time of discharge from ICU*
- time until criteria for “fit for discharge from hospital” are fulfilled (hospitalization release criteria according to Marshall et al., 1999, Marshall and Chung, 1997) *surveyed once daily on ICU respectively surgical ward (if fit-for-discharge criteria are not fulfilled within the 5th postoperative day it will be controlled until fulfillment or until end of study, whatever occurs first)*
- Complication rate - surgical complications such as re-do surgery (e. g. anastomotic insufficiency or bowel leakage), disturbed wound-healing or medical complications which delay time to fully oral nutrition – *documentation at the study end*
- combined outcome parameter of prolonged length of stay (based on mean length of stay according to the German Diagnosis Related Group System D-DRG) or death (determination will be when DRG-data are available, i. e. after study end)
- Health Related Quality of Life (HRQoL) according to the EQ-5D questionnaire – *measurement baseline and 3 months after surgery*

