### **Post-operative patient management**

A standardised therapy management with respect to enteral nutrition, mobilisation etc will be applied and documented in detail in the CRF.

On ICU volume replacement will be performed at the discretion of the attending physician. See “unauthorised concomitant medication”.

For the assessment of the second primary variable, time until fully on oral diet, it has to be assessed for a period of maximally 15 days. It will be assessed for each day (on the subsequent day) whether the patient receives parenteral nutrition. As soon as the patient is off parenteral nutrition and has taken nutrients via oral (not enteral) pathway at least three times that day no further recording of nutritional diet is required.

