## **12 DEFINITION OF THE PRIMARY AND SECONDARY VARIABLES**

### **12.1 Primary Variable**

First primary endpoint: Intraoperatively required amount of HES (mLs) under target controlled volume replacement therapy.

Second primary endpoint: Time until fully on oral (solid) diet (days): Fully on oral (solid) diet is reached when no more parenteral and enteral nutrition is given and the patient has taken nutrients via the oral pathway for at least three times that day.

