## **15 DURATION OF STUDY AND STUDY SCHEDULE**

### **15.1 Duration of study per patient**

Start of study: with randomisation

Treatment period (infusion of Investigational Products):

During surgery (guided by oesophageal Doppler measurements)

End of study: Postoperative day 15 or hospital discharge, whatever occurs first

Last evaluation of certain parameters will be 3 months post-surgery respectively when DRG data are available.

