## **16 STATISTICS**

### **16.1 Statistical methods**

This section gives an overview of the statistics planned for the study. All programming of tables, figures, listings and statistical analyses will be performed using the statistical software packages SPSS® version 13, SAS® version 9.1.3 and StatXact® version 6.

A Statistical Analysis Plan (StAP) will be finalized before close of database. It includes all protocol amendments. In case a protocol amendment is passed after finalization of the StAP an amendment to the StAP is to be composed.

All target criteria (primary and secondary variables) will first be examined by exploratory data analysis and descriptively evaluated (Wernecke 1995). In this setting, the evaluation of structural homogeneity of the treatment groups will be performed for the purpose of quality assurance.

A multiple primary endpoint consisting of “amount of HES-solution in ml” (first primary variable) and “days until fully on oral (solid) diet” (second primary variable) is defined. The principle of ordered hypothesis will be used (Hothorn and Lehmacher, 1991)(Maurer et al., 1995) for testing the two primary efficacy parameters. If the first primary hypothesis will result in a statistically significant difference of the amount of the hyperoncotic HES-solution as compared with the amount of iso-oncotic HES-solution, the second primary variable will be analyzed using the same procedure (with an unchanged error of the 1st kind  $\alpha = 5\%$ ) as described for the first primary variable.

The two primary variables will be evaluated with a non-parametric statistical test (Mann-Whitney U-test, Hartung and Elpelt, 1993) taking into consideration small sample sizes and possible deviation from normal distribution. Stratification variables will be included in the primary analysis as covariates (in a nonparametric analysis of covariance cf. Bathke, Brunner 2003).

Secondary target variables will also be evaluated with nonparametric tests according to their scaling. Whereby, in case of a small random sample size or an unbalanced condition, exact tests will be used (Mehta, Patel, 1998).

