### **16.8 Patient selection for analyses**

An Intent-To-Treat (ITT) analysis and Full Analysis Set (FAS) respectively is planned as primary.

Additionally, an Per-Protocol (PP) or Valid Case Analysis Set (VCAS) respectively will be performed i. e. all patients where none of the following events occurred:

- Stop of treatment due to adverse reaction
- severe violation of study protocol

The results of both analyses will be compared and possible differences have to be discussed accordingly.

The definitions for any population groups chosen for analysis (e.g. all patients randomized, intent-to-treat, per-protocol, completers) will be provided in the statistical analysis plan. Decision on analysis of the respective study population will be performed prior unblinding.

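### Time to full oral diet has no value for patients who do not reach it by day 15, die first or are discharged first, and the no-imputation rule, read literally, drops them from the rank test

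*Protocol*

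**What the plan says.** Section 12.1 makes the second primary endpoint an event that has to be reached: "Fully on oral (solid) diet is reached when no more parenteral and enteral nutrition is given", together with oral intake at least three times that day.

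Observation is capped. Section 11 (post-operative patient management) says of this endpoint that "it has to be assessed for a period of maximally 15 days". Section 15.1 closes follow-up with "End of study: Postoperative day 15 or hospital discharge, whatever occurs first". For the gastrointestinal times, the synopsis specifies "measurement daily from post-op day +1 until fulfilment or until end of study, whatever occurs first". None of these places says what is entered if the event has not occurred.

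Section 16.1 fixes the test: "The two primary variables will be evaluated with a non-parametric statistical test (Mann-Whitney U-test", with the stratification variables as covariates in a nonparametric analysis of covariance. Either method needs a value or a rank for every patient analysed.

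Section 16.5 says that "all patients who are randomized will be included in the primary analysis" and, in the same sentence, that "in those instances where data are missing, missing values will not be imputed". Section 16.8 adds: "An Intent-To-Treat (ITT) analysis and Full Analysis Set (FAS) respectively is planned as primary".

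**The concern.** Three kinds of patient have no number of days: those still on parenteral or enteral nutrition at day 15, those who die before reaching full oral diet, and those discharged before reaching it. If the no-imputation rule is applied to them, they leave the rank test. The exclusion then depends on the outcome, because the patients lost at day 15 are those with the longest times. Yet all that a rank test needs about them is known: they did worse than everyone who reached the endpoint by day 15.

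Such patients are foreseen. The synopsis and section 12.3 list complications that delay full oral nutrition, and include death in a combined outcome.

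A treatment that prevents very slow recovery would lose part of its effect. A treatment with more failures could look neutral, or even faster, among those who succeed. The endpoint is confirmatory, so the rule has to be unambiguous before unblinding.

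**Working it through.** **Inputs.** Section 16.4: difference 1.5 days, effect size 0.698, 69 per group, stated power 97%, and 37 per group for 80% power. Section 16.2: two-sided 5%. The implied SD is 1.5 / 0.698 = 2.15 days. The document gives neither the mean time to full oral diet nor the share beyond day 15, so both are assumed over a range.

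**The plan's own figure.** For a normal shift d, the Noether formula uses p = Φ(d/√2) and n per group = (z₀.₉₇₅ + z₀.₈₀)² / [6(p − 0.5)²].

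- p = Φ(0.698/√2) = 0.689
- n = (1.960 + 0.842)² / (6 × 0.1892²) = 36.5, so 37, as stated
- power at 69 = Φ(√(6 × 69) × 0.1892 − 1.960) = Φ(1.89) = 97.1%, as stated

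The sample-size figures are therefore correct, provided that all 69 patients per group have a value.

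**Effect of deletion under the planned effect.** Simulation with 3,000 trials per row, 69 per arm, normal times with SD 2.15, a 1.5-day shift, and days rounded up. Deletion removes patients beyond day 15. Worst rank gives them one common value above 15. The share of controls beyond day 15 is 1 − Φ((15 − mean)/2.15); for a mean of 12 this is 1 − Φ(1.40) = 8%.

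| Assumed control mean (days) | Beyond day 15, control / test | Power, deletion | Power, worst rank |
|---|---|---|---|
| 9 | 0.3% / 0% | 97% | 97% |
| 11 | 3% / 0.5% | 97% | 98% |
| 12 | 8% / 2% | 94% | 98% |
| 13 | 18% / 5% | 87–89% | 97–98% |
| 14 | 32% / 12% | 74% | 97% |

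The spread in the fourth row is simulation error: √(0.88 × 0.12 / 3,000) is about 0.6 percentage points.

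**Arms that differ in non-attainment (rates assumed).**

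- Equal times among those who reach the endpoint, non-attainment 10% vs 25%: the test rejects in about 5% of trials with deletion and 33% with worst rank. At 10% vs 30% the figures are about 5% and 55%. Deletion cannot see the difference.
- Extreme case: non-attainment 35% in the HES 10% arm vs 15% in the HES 6% arm, with HES 10% patients 1 day faster among those who reach the endpoint. Deletion significantly favours HES 10% in 60–64% of trials. Worst rank is significant in 9–11%, and favours HES 10% in under 1%.

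**Cost of worst rank.** With 20% non-attainment in both arms, unrelated to treatment, and the 1.5-day shift among the rest, power falls from about 95% to 70%.

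**The case against.** A reader might infer that the protocol prescribes deletion of the worst outcomes. It does not say so. A patient still on parenteral nutrition at day 15 has been checked daily, and the observed status, not reached, is not obviously missing data. The first half of the section 16.5 sentence and the ITT/FAS statement in section 16.8 both point to inclusion. A statistical analysis plan is due before database close and could rank these patients last without contradicting the endpoint definition. This stands in part: deletion is a consequence of the literal text, not a stated intention. But the protocol does not leave missing data open. It states a rule, offers no other for these patients, and contradicts itself within one sentence.

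A reader might also infer that a large power loss is to be expected. More skewed recovery times do give one: lognormal times with medians of 8 vs 10 days and a log-scale SD of 0.5 give 46% with deletion and 71% with worst rank. Those distributions have SDs of about 4.8 and 6.0 days, more than twice the planning value. Under the planning values, deletion keeps power above the 80% target even with 18% of controls beyond day 15. Likewise, nothing in the document supports a 20-point imbalance in non-attainment; those scenarios show the mechanism, not its expected size.

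Finally, this endpoint is tested only after the first is significant, and the first sets the sample size. That limits the reach of the problem, but the second test remains confirmatory at the full 5%.

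**Conclusion.** The point holds as a gap and a contradiction. A confirmatory endpoint has no value for non-attainers by day 15, for deaths before attainment, or for discharges before attainment. The only stated rule, taken literally, excludes them by outcome, against the same sentence's promise to include every randomised patient.

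The size is not known from the document. Under the planned shift and SD it runs from negligible (up to about 3% of controls beyond day 15) to a fall from about 97% to 74% (32% of controls). Bias in either direction needs non-attainment to differ between arms, which is possible but assumed here. The power and sample-size figures in section 16.4 are not wrong; they presuppose a value for every patient.

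**What to change.** - **Section 12.1:** define the endpoint for the rank test so that every patient in the ITT/FAS who has not met the definition by day 15, or who dies before meeting it, receives one common rank worse than day 15. Do not narrow this to treated patients without saying so, because section 16.5 speaks of all randomised patients.
- **Early discharge:** state one primary-analysis rule for patients discharged before meeting the definition, for example the same common rank. Add a censored-data rank test (Gehan-Wilcoxon, censored at discharge) as a sensitivity analysis, since these patients were not observed to day 15.
- **Section 16.5:** keep the no-imputation rule for data that are truly unobserved, and say that it does not apply to the patients above. Assigning a defined rank is part of the endpoint, so the sentence need not be deleted.

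The cost is wording only, settled before unblinding, with no added data collection. The statistical price is the loss of power from ties when non-attainment is unrelated to treatment, shown in the working.

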## **16.6 Interim Analysis**

Not applicable.

The confirmation respective recalculation of sample size for the first primary variable and assurance of power for the second primary variable after inclusion of 60 patients will only be performed by estimating the pooled variance (without unblinding). (Refer to section 16.4)

### **16.7 Criteria for the termination of the study**

If after pilotphase (after 60 patients) the calculation of the pooled variance reveals that the estimated total number of 228 patients will be exceeded the study will not be carried on but stopped for futility after the pilot phase.

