## 16.2 Level of significance and power

All tests will be conducted with an error of 1st kind  $\alpha = 5\%$ , two-sided.

Tests of secondary variables will be carried out in the area of exploratory data analysis. Therefore, corresponding p-values are to be regarded as exploratory ones and no adjustments for multiple testing will be made.

Sample size calculations are to be performed with a power of 80%

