## 16.4 Sample Size

The first primary variable, i. e. amount of plasma volume replacement therapy (in addition to a basal electrolyte infusion), will serve to calculate sample size. It is assumed that 250ml difference between the two HES treatment arms is clinically relevant.

It is roughly calculated that 228 patients shall be included which is based on the following assumptions: 69 patients per group, supposing an effect size (difference of means/(common standard deviation) =  $\frac{1}{2} = 0.5$ , error of the 1st kind  $\alpha = 5\%$  (two-sided), Power = 80% and the nonparametric Mann-Whitney U-Test (Calculations with

nQuery Advisor, version 6.0). Taking the drop-out rate of 10% into consideration, a sample size of 76 patients per group will be needed.

However, at present no reliable information is available on the amount of plasma volume requirement in elective pancreatic surgery. Thus, an internal pilot phase including 60 patients (including drop-outs) will be performed in order to re-calculate total sample size. For re-calculation the pooled variance will be assessed on the grounds of clinical relevant difference without unblinding. Type I error for both phases of the study will strictly be maintained. (Kieser and Friede, 2000 and 2003)

For the second primary endpoint it is assumed that 1.5 day difference between the two treatment arms will be achieved. Based on hospital's own data an effect size (difference of means/ common standard deviation) of 0.698 is calculated which reveals that inclusion of 69 patients – as for the first primary endpoint (without dropouts) – will lead to a power of 97%. A sample size of only 37 (per group) is demanded to achieve a power of 80%. Therefore, enough power is ensured to prove the second primary endpoint after significance of the first. After pilot phase, the re-estimation of the (pooled) variance will also be accomplished for the second primary variable in order to ensure a sufficient power comparing the two treatments with the former re-calculated sample size (see above).

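### The stop-for-futility threshold of 228 equals the planned sample size, so the rule has no margin and would end a correctly planned trial about half the time

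*Protocol*

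**What the plan says.** Protocol section 16.4 takes the amount of HES as the variable that sets the sample size. "It is assumed that 250ml difference between the two HES treatment arms is clinically relevant". The calculation is "69 patients per group, supposing an effect size (difference of means/(common standard deviation") of 0.5, with two-sided 5% error, 80% power and the Mann-Whitney test. It continues: "Taking the drop-out rate of 10% into consideration, a sample size of 76 patients per group will be needed". Three groups of 76 give 228, which the section itself treats as approximate: "It is roughly calculated that 228 patients shall be included".

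The same section explains why there is an internal pilot of 60 patients: "at present no reliable information is available on the amount of plasma volume requirement in elective pancreatic surgery". The variance is to be re-estimated without unblinding, with the relevant difference held fixed, and the total recalculated. The note to the design figure in section 8 says that the total may change as a result.

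Section 16.7, repeated in 9.4.1, then fixes the consequence: if the pilot variance shows that "the estimated total number of 228 patients will be exceeded the study will not be carried on but stopped for futility". Neither section gives a tolerance, a higher ceiling, a power floor or room for judgement.

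**The concern.** The trigger and the planned number are the same figure. A pilot SD that lies above the guessed value by almost any amount orders a stop, and an SD estimated from a few dozen patients falls above or below its true value nearly at random. The pilot exists because the SD is not known, yet the rule penalises the plan for the guess being even slightly low.

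The label is also wrong. The re-estimation looks only at a blinded variance (section 16.6), so it says nothing about whether the hyper-oncotic solution works. A recalculated number a little over 228 means only that 228 patients would give a little under 80% power for 250 mL. At stake is the loss of a sound trial after 60 patients have been randomised. In addition, the recalculated number can be confirmed or lowered but never raised above 228, so the re-estimation cannot protect power when the SD is larger than guessed.

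**Working it through.** **Inputs.** From sections 16.2, 16.4 and 8: difference 250 mL, effect size 0.5, two-sided 5%, power 80%, drop-out 10%, allocation 1:1:1, pilot of 20 per arm including drop-outs. Derived: implied SD = 250/0.5 = 500 mL (the protocol does not state it). Assumed: normal data, and 18-20 evaluable patients per arm in the pilot.

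**1. Reproduce 228.** Noether's formula for the Mann-Whitney test is n = (1.960 + 0.842)² / [6(p − 0.5)²], with p = Φ(d/√2).
- At d = 0.5, p = 0.6382 and n = 68.53, so 69 per group.
- 69 × 1.1 = 75.9, so 76; 3 × 76 = 228. The plan's figure is reproduced.

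**2. Find the margin.** With 250 mL fixed, n reaches 69 at SD 501.8 mL, or 1.007 times the planned variance. At SD 502 mL, n = 69.06, so 70; 70 × 1.1 = 77; 3 × 77 = 231, and the trial stops. Power with 69 per group is then 79.97%.

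**3. Probability of stopping when every assumption holds (SD 500 mL, difference 250 mL).**
- *Within-arm pooled variance of the two HES arms:* P(χ²/df > 1.007) = 45.6% on 34 df (18 per arm) and 45.7% on 38 df (20 per arm).
- *Blinded variance of the two HES arms lumped, corrected for the 250 mL difference* (simulation): 45-46%.
- *The same, uncorrected* (simulation): 56-57%. The difference between arms inflates the expected variance to about 500² + 250²/4, an SD of about 516 mL. That alone implies 73 per group, then 81 with drop-out, and 243 in total.
- *Right-skewed (gamma) volumes, within-arm, assumed means 750-2000 mL:* 43-45%.
- *All three arms lumped:* about 57% if the crystalloid mean equals the higher HES mean, and about 94-95% if it lies an assumed 500 mL above it.

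**4. Sensitivity to the true SD.** Power is for 250 mL with 69 evaluable per group.

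| True SD (mL) | P(stop), within-arm, 34-38 df | Power at 228 |
|---|---|---|
| 400 | 1-2% | 94% |
| 450 | 14-16% (24% lumped, uncorrected) | 87% |
| 475 | 29% | 84% |
| 500 | 46% | 80% |
| 525 | 61-62% | 76.5% |
| 550 | 74-76% | 73% |
| 600 | 91-92% | 65% |

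**5. Second primary endpoint.** Its planned need is 37 per group, so its variance would have to be 1.96 times the planned value before 69 is passed (probability below 0.1%). It adds almost nothing to the risk of stopping.

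**6. An example floor.** Power at 69 per group falls to 60% at SD 640 mL. If the trial stopped only above that pilot SD (within-arm), P(stop) would be about 1% at true SD 500 mL and 26% at 600 mL. At true SD 700 mL, where power is 53%, the trial would still continue about 25% of the time.

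**The case against.** The strongest defence is that this is the sponsor's choice. The rule is stated openly and in the same terms in both sections. It is applied blind, so it neither inflates type I error nor biases the estimate, and a sponsor may decline to exceed 228 patients or to run below 80% power. That stands as a reason not to go above 228. It does not explain why a trial that would have 77-79% power at 228 should be abandoned, and it does not make a variance check a futility analysis.

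It is also fair that the near-even odds rest on a derived SD of 500 mL in a calculation that the protocol calls rough, and that the estimator is not specified. A true SD well below 500 mL makes a stop unlikely. The range of results shows this, and the lack of margin does not depend on it.

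Three stronger readings are not supported:
- A reader might infer that the trial will probably be abandoned. That depends on the true SD. Even at 500 mL, the within-arm figure is slightly below one half.
- A reader might infer that the re-estimation can only shrink or end the trial. Confirmation at 228 is a stated outcome; what is excluded is an increase.
- A reader might divide by 0.9 for drop-out (69/0.9, so 77 per group and 231 in total) and say that the plan already breaches its own limit. The plan multiplies by 1.1, which gives 76 and 228, and 228 is not exceeded.

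**Conclusion.** The point holds and should be fixed. The rule leaves a margin of about 2 mL on an implied SD of 500 mL. With all planning assumptions true, it stops the trial with probability of about 46% (within-arm or difference-corrected variance) to 56-57% (uncorrected, two HES arms lumped). These figures rest on normal data and 18-20 evaluable patients per HES arm. The protocol does not say whether two or three arms are pooled, nor whether the variance is corrected for the difference. Adding a crystalloid arm with a higher mean, which section 8 leads one to expect, would raise the probability. The exact figure is therefore uncertain, but the absence of a margin is not.

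**What to change.** In sections 9.4.1 and 16.7, make 228 a cap. If the recalculated number exceeds 228, continue to 228 and report the power attained for 250 mL. Stop only if the recalculated power at 228 falls below a prespecified floor chosen by the sponsor; 60%, a pilot SD above about 640 mL, is one example. Call this a feasibility stop, and bring the futility wording in the synopsis and section 8 into line. In section 16.4, state which arms enter the blinded variance, which estimator is used and whether it is corrected for the assumed difference, because the stop limit depends on this.

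The cost is protocol wording, with no patients beyond the 228 planned. The downside is that the trial may complete with less than the 80% power set in section 16.2, and occasionally with less than the floor itself, because the pilot SD is imprecise.
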